### Inclusion criteria

Eligibility requirements will include the following: male and female patients who are more than 50 years old and who have knee OA diagnosed according to the American College of Rheumatology classification criteria (with at least one osteophyte in the tibiofemoral joint and with a Kellgren-Lawrence grade of more than 2), who have had a history of moderate or greater knee pain of more than 3 months’ duration and have reported moderate or greater, clinically significant, knee pain during most days of the last month before the interview, and who have given their consent to participate in the study. Patients will be selected among those who are not on the waiting list for total knee arthroplasty by the traumatology unit of our hospital.

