### Participants

Participants will be selected from a population with knee chronic pain caused by OA (>3 months in duration), from the communities of the island of Mallorca (Balearic Islands, Spain). These participants will be recruited in the outpatient clinics of the island’s hospitals and advertisements in local newspapers and through the hospital website (http://www.hsll.es). Advertisements for patient recruitment will not specify acupuncture as one of the treatments being investigated or offered. Doctors from the trauma services of local hospitals will be invited to screen patients. The clinical trial will be performed by the Pain Unit at Son Llàtzer Hospital, Palma de Mallorca.

A total of 160 patients will be necessary (80 subjects for each treatment group) to detect differences of at least three points in the pain perception assessment according to VAS (scale of 0 to 10). Accepted values will be for an alpha risk of 1 % and beta risk of less than 5 % in a bilateral contrast as well as a value of 4 for the standard deviation (size effect of 0.75). It is assumed that 20 % of the trial patients will be lost to attrition. Patients will be included in the study by case-consecutive, non-probability sampling after responding to a recruitment visit to the Pain Clinic; then if they sign an informed consent form, they will be placed randomly into one of the treatment groups [30].

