### Removal criteria

Patients will be removed by voluntary removal or by failure to consecutively attend two or more EA sessions.

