### Variables

#### Main variables

The primary outcomes will be the changes from the baseline of the VAS and the Western Ontario and McMaster Universities Osteoarthritis Index (WOMAC) for pain at the completion of treatment at 12 weeks.

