#### Secondary variables

Secondary variables to be considered are the following: the change in the secondary efficacy variables from the baseline of the Short Form 36 version 2 health survey (SF-36v2) (patient-perceived quality of life), the change in plasma cortisol and beta-endorphin levels, the scores for the Goldberg Anxiety and Depression Scale (GADS), changes in pain medication use, changes in functional capacity and stiffness (WOMAC subscales), and VAS scores measured at 1 month, 3 months, 6 months, and 1 year after study commencement.

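### The arthroplasty waiting-list rule covers one hospital while recruitment covers the whole island, so patients listed for knee replacement elsewhere can be enrolled

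*Protocol article*

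**What the plan says.** The Participants section of the protocol article sets a wide recruitment area. Patients will be "recruited in the outpatient clinics of the island’s hospitals and advertisements in local newspapers", with the hospital website as a further channel. It adds: "Doctors from the trauma services of local hospitals will be invited to screen patients". Treatment and follow-up take place at one site: "The clinical trial will be performed by the Pain Unit at Son Llàtzer Hospital, Palma de Mallorca".

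The Inclusion criteria ask for radiographic disease "with a Kellgren-Lawrence grade of more than 2" and moderate or greater knee pain. They close with the arthroplasty rule: patients must be "not on the waiting list for total knee arthroplasty by the traumatology unit of our hospital".

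The Exclusion criteria do not mention arthroplasty, planned surgery or any other hospital's list. The Procedure section has eligibility checked again when the patient arrives at the pain clinic, but against the same criteria. Under Removal criteria, "Patients will be removed by voluntary removal or by failure to consecutively attend two or more EA sessions"; surgery is not named.

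The primary outcomes are the changes in VAS and WOMAC pain "for pain at the completion of treatment at 12 weeks" (Main variables). The secondary outcomes are "measured at 1 month, 3 months, 6 months, and 1 year after study commencement" (Secondary variables).

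**The concern.** The safeguard and the recruitment area do not match. Recruitment draws on several hospitals, and their trauma services are asked to screen, but the waiting-list rule looks at one hospital's list only. A patient waiting for a knee replacement at any other recruiting hospital passes every stated criterion.

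Such a patient could be operated on within the year of follow-up. Replacing a study knee changes the source of the pain being measured, so later VAS, WOMAC, SF-36v2 and analgesic-use values would reflect the operation as well as the allocated treatment. If the patient leaves the trial instead, those values are lost. In either case the later comparisons say less about electro-acupuncture.

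This is not a detail left to an analysis plan. The criterion is stated, and it is stated too narrowly for the recruitment described. An analysis plan can say how surgery during follow-up is handled, but it cannot change who was eligible.

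**Working it through.** **Step 1: the text side by side**

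| Element | Scope | Section |
|---|---|---|
| Recruitment | Outpatient clinics of the island's hospitals, newspapers, hospital website | Participants |
| Screening doctors | Trauma services of local hospitals (plural) | Participants |
| Arthroplasty rule | Waiting list of the trial hospital's traumatology unit | Inclusion criteria |
| Exclusions | Arthroplasty not mentioned | Exclusion criteria |
| Re-check | Same selection criteria applied again | Procedure |
| Removal | Voluntary, or two or more consecutive missed sessions | Removal criteria |

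No row extends the arthroplasty rule beyond one hospital.

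**Step 2: what surgery would do under the session schedule** (Intervention; Table 1)

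- Month 1: two sessions per week. An absence of about a week misses two in a row and meets the removal rule, before the 12-week primary time.
- Months 1 to 3: one session per month. Missing two in a row needs an absence covering two sessions a month apart.
- Months 3 to 6: one session every 45 days. The absence must span at least 45 days.
- Months 6 to 12: one session every 2 months. The absence must span at least 2 months.

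Early surgery would therefore probably lead to removal. Later surgery might cost one session or none, so the patient could stay in and contribute post-operative scores at 6 months or 1 year.

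**Step 3: the plan's own sample size**

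Inputs from Participants: difference 3 points, SD 4, two-sided alpha 0.01, beta below 0.05 (power taken as 0.95), attrition 20%.

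n per arm = 2 × (z₀.₉₉₅ + z₀.₉₅)² × (SD/difference)² = 2 × (2.576 + 1.645)² × (4/3)² ≈ 63.3, rounded up to 64.

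64 / (1 − 0.20) = 80 per arm, 160 in total. The stated figure reproduces, and power with 64 evaluable per arm is 0.952.

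**Step 4: illustration of sensitivity**

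The protocol gives no arthroplasty rate, so the first column is an assumption: the share of each arm operated on before the analysed visit, in addition to the 20% attrition.

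- Data unusable: n per arm = 80 × (1 − 0.20 − share), rounded down; difference stays at 3.
- Data kept: n per arm = 64; difference = 3 × (1 − share); SD unchanged.
- Power = Φ(difference/SD × √(n/2) − 2.576).

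| Assumed share | n per arm, unusable | Power, unusable | Diluted difference | Power, kept |
|---|---|---|---|---|
| 0% | 64 | 0.952 | 3.000 | 0.952 |
| 2.5% | 62 | 0.945 | 2.925 | 0.941 |
| 5% | 60 | 0.937 | 2.850 | 0.927 |
| 10% | 56 | 0.918 | 2.700 | 0.893 |
| 15% | 52 | 0.894 | 2.550 | 0.849 |

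Any given share is less likely to have been reached by 12 weeks than by 6 months or 1 year, because less time has passed.

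**The case against.** **Randomisation protects the comparison.** Patients listed at baseline are allocated 1:1, so they are balanced on average. This stands. A reader might infer that the treatment comparison is biased, but listing alone does not bias it. Bias needs the decision to operate to depend on response. If less-relieved patients went ahead more often, post-operative improvement would accrue to the worse-performing arm and hide part of a difference. The protocol neither shows nor rules this out.

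**The primary outcome is little exposed.** This also stands. The Main variables section places it at 12 weeks, and the 6-month and 1-year comparisons are secondary.

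**The attrition allowance may absorb the loss.** The plan already allows for 32 losses (20% of 160). Losses from surgery may fall inside that number, whereas the table above adds them on top. This stands for lost data, but the allowance does nothing for patients who stay in with a replaced knee.

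**A size cannot be given.** A reader might suppose that half of the 160 come from outside the trial hospital and that 5–15% of those are listed, giving 80 × 0.05 = 4 to 80 × 0.15 = 12 patients, or 12.5–37.5% of the 32 planned losses. The documents support neither share. They also give no waiting time or operation rate, so the step from listed to operated on to lost is unsupported too.

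**Surgery does not automatically mean removal.** Step 2 confirms this. The removal rule needs two consecutive missed sessions, which is easily met in month 1 and much less so later.

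**The motive and the severity link are inferred.** The protocol gives no reason for the waiting-list rule and does not relate radiographic grade to listing. The point needs neither.

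**The article is condensed.** A fuller protocol may exist. That carries little weight here, because the criterion names a single hospital explicitly.

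**Conclusion.** The mismatch is real and follows from the wording alone: patients already listed for knee replacement at another hospital are eligible and could be operated on during the 1-year follow-up. The expected consequence is dilution, extra variability and missing data, chiefly at 6 months and 1 year. Systematic bias is conditional on surgery depending on treatment response.

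The number of patients affected is unknown. The power figures are illustrations that rest on assumed operation shares, proportional dilution, an unchanged SD and losses added to the full attrition allowance. Within that range the effect is modest: at an assumed 2.5–10%, power stays between 0.945 and 0.918 if data are lost, or between 0.941 and 0.893 if they are kept.

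A reader might conclude that the sample size is wrong or that the primary analysis is compromised. Neither follows. The 160 reproduces from the stated inputs, and exposure at 12 weeks is limited. This is an inexpensive improvement to a stated criterion.

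**What to change.** Align the arthroplasty criterion with the recruitment area: the patient is not on a waiting list for, or scheduled for, arthroplasty of a study knee (either knee, where both are treated) at any hospital. Ask at visit 0 and again at the eligibility re-check that the Procedure section already provides for.

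The cost is one wording change, one screening question and a few more screen failures. The sample size, visits and planned tests do not change. Two limits should be acknowledged. Patients listed after enrolment are not covered; how their data are analysed may be set out in a plan that is not shown. And because the Trial status section reports recruitment as already under way, the change protects only patients not yet enrolled.

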### Exclusion criteria

Patients with any of the following will be excluded from the study: a history of any secondary OA associated with any systemic arthropathy (i.e., rheumatoid arthritis or gouty arthritis); any knee treatment with steroids, methotrexate, or azathioprine; recent traumatisms caused by acupunctural insertion; a history of bleeding disorders or any disease related to acupuncture contraindications; a history of any knee injection in the previous 6 months (e.g., cortisone and hyaluronic acid); an acupuncture treatment history; or a history of morphine or morphine derivative use.

### Removal criteria

Patients will be removed by voluntary removal or by failure to consecutively attend two or more EA sessions.

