### Procedure

Figure 1 describes the trial protocol. The eligibility of prospective participants will be determined by a researcher who is not involved in the assessment or treatment of the participants. Ethical approval was obtained from the Balearic Islands Human Research Ethics Committee in July 2013 (CEI-IB, #IB 2077/13 PI).

Upon arrival at the Clinic for Pain Treatment, recruited patients will be informed once again about the trial objectives, and any questions or doubts that the patient might still have with respect to the study will be resolved. Patients will then be informed that they are testing a new EA technique for knee pain treatment. Placebo or sham acupuncture (SA) will not be mentioned to the patient during the interview or referred to in the informed consent form. Subjects will be placed into one of two study groups (with a strict 50 % probability), and to reinforce and encourage treatment follow-up, patients will be told that the effects are to be perceived over the medium- to long-term time frame. Patients will be re-assessed to ensure that they still comply with the selection criteria and that they have not acquired any new criteria for exclusion. Participants will provide informed consent in the first baseline visit (Table 1).

**Table 1 Tab1:** Planned visit schedule for treatment and follow-up, indicating visit number and frequency

	Visits									
	0	1st	2nd -7th	8th	9th	10th	11th	12th	13th-14th	15th
			(2 weekly /month)	(follow-up 1st month)	(2nd month)	(follow-up 3rd month)	(every 45 days)	(follow-up 6th month)	(every 2 months)	End of follow-up (1 year)

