##### Control group (group B)

A valid method of placebo acupuncture with non-insertion of the needle will be used for the control group [35]. Two needles will be inserted into the sham points of the abdominal area in the same position used for group A, approximately 3 cm lateral to and slightly above the umbilicus bilaterally, and then two pieces of adhesive tape will be immediately taped next to the needles. In addition, a mock plastic needle guide tube will be placed on the surface of each of the nine true points in the leg so that some discernable sensation will be produced; then a needle will be immediately applied without needle insertion to the dermal surface at each point and will be retained at this position for 20–30 min. These plastic guide tubes will be applied in the same manner as for group A in order to produce the same perceptible sensation.

The control group will receive the same session and schedule as group A. This will include the same active needle placements, although needle insertion will not occur at these nine points (local and distal points). Not only will the accessories of the EA equipment be connected in the same point in group A without electric stimulation, a mock transelectrical stimulation unit (which emits a “timer” sound and has a blinking light) will be attached to the sham needles at the knee.

To facilitate patient blinding for both groups, a screen will be placed below the abdomen to prevent participants from actually observing true or sham procedures at the knee area but at the same time will permit them to see the procedure that is being given in the abdominal area. It is important to state that this type of intervention will need some time for the results to be noted, and a thorough follow-up is necessary to avoid dropouts from both groups.

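### The removal rule does not separate missing sessions from leaving outcome follow-up, so randomised patients can be lost before the 12-week primary assessment and the comparison can be biased

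*Protocol article*

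**What the plan says.** The whole of the Removal criteria section is one sentence: "Patients will be removed by voluntary removal or by failure to consecutively attend two or more EA sessions". It follows directly on the inclusion and exclusion criteria and puts non-attendance beside voluntary withdrawal.

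Other parts of the protocol article bear on it:

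- **Schedule (Intervention; Table 1).** Two sessions a week for four weeks (visits 1 to 8), one in month 2 (visit 9), one in month 3 (visit 10), then every 45 days to month 6 and every two months to one year. The control arm follows the same schedule.
- **Assessments (Table 1; At 1 month's time).** After baseline, outcomes are taken at visits 8, 10, 12 and 15, each of which is also a treatment visit. At one month the forms are completed just before that day's session. Reasons for dropout are recorded at these four visits.
- **Primary outcome (Main variables).** Change from baseline in VAS and WOMAC pain at 12 weeks.
- **Attrition.** The Participants section assumes that 20% "of the trial patients will be lost to attrition". The Control group section says that "a thorough follow-up is necessary to avoid dropouts from both groups".
- **Analysis (Statistical analysis).** Tests are named; no analysis population is.

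**The concern.** Missing sessions is an event after randomisation. If it ends a patient's participation, the 12-week comparison is between those who kept attending, not between the groups as randomised. Attendance may depend on how a patient is doing and how the sessions feel, and these may differ between needling with current at the maximum tolerable intensity and a procedure with no insertion or current at the knee. The sample size allows for the loss of numbers, but extra numbers do not remove selection.

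This is not something that can be left to the analysis plan. If a removed patient's 12-week VAS and WOMAC pain are never collected, a later plan can only impute them.

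**Working it through.** **1. The plan's own figure.** The Participants section gives the total: "A total of 160 patients will be necessary (80 subjects for each treatment group"). The target there is a 3-point VAS difference with an SD of 4, so 3/4 = 0.75 SD. The error rates are set as follows: "Accepted values will be for an alpha risk of 1 % and beta risk of less than 5 % in a bilateral contrast".

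- n per arm = 2 × [4 × (2.576 + 1.645) / 3]² = 63.3, rounded up to 64.
- With 20% attrition: 64 / 0.80 = 80 per arm, 160 in total. The figure is reproduced exactly.

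Power therefore rests on the 64 per arm who remain (95.2%). This fits removed patients having no outcome, though it does not prove it.

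**2. When the rule can act before the primary assessment.** I take the 12-week assessment to be the month-3 visit (visit 10).

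- Two consecutive absences within visits 1 to 8: one missed week is enough. Removal falls at week 4 or earlier, so eight weeks or more before the assessment.
- Visits 8 and 9 missed: removal falls at month 2, about a month before it.
- Visits 9 and 10 missed: the scheduled primary assessment has itself been missed.
- Later absences affect only the 6- and 12-month time points.

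The avoidable loss of primary data thus comes mainly from month 1.

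**3. Illustration of bias.** The protocol gives no removal rates by arm and no relation between attendance and outcome, so both are assumed. Take a normal outcome with SD 4 and no true effect. The fraction p removed is the upper tail of a latent variable with correlation ρ to a worse outcome. The mean of the retained patients then shifts towards improvement by ρ × 4 × φ(c) / (1 − p), where c is the (1 − p) normal quantile. The bias is the difference in shift between arms. Rejection is for a two-sided 1% test with SE = 4 × √(1/n₁ + 1/n₂) and n = 80(1 − p).

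φ(c)/(1 − p) is 0.195 at 10%, 0.274 at 15%, 0.350 at 20%, 0.424 at 25% and 0.497 at 30%.

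| Removal, one arm v the other | ρ = 0.3 | ρ = 0.5 |
|---|---|---|
| 20% v 20%, same mechanism | 0 points; 1.0% | 0 points; 1.0% |
| 15% v 25% | 0.18 points; 1.2% | 0.30 points; 1.7% |
| 10% v 30% | 0.36 points; 2.0% | 0.60 points; 4.2% |
| 20% v 20%, outcome-related in one arm only | 0.42 points; 2.4% | 0.70 points; 5.7% |

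With ρ = 0 the bias is 0 at any rates. Worked example for 10% v 30% and ρ = 0.5: 0.5 × 4 × (0.497 − 0.195) = 0.60.

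In the last row, shift = p × D, where D is how much worse removed patients did than retained ones. So D = 0.42/0.20 = 2.1 points at ρ = 0.3 and 0.70/0.20 = 3.5 points at ρ = 0.5. The upper end is a demanding assumption.

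**Direction.** The arm that loses more of its poor responders looks better than it should. If that is sham, the bias works against EA; if it is EA, in its favour.

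**4. Cost of keeping everyone.** With 80 per arm analysed, power for the full 3 points is 98.5%. If a fraction f gets no benefit (an assumption), the effect is 3(1 − f):

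- f = 10%: 2.7 points, power 95.5%
- f = 20%: 2.4 points, power 88.9%
- f = 30%: 2.1 points, power 77.2%

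**The case against.** The text says only that patients are removed, not from what. It may mean no more than that sessions stop, with assessments continuing. No analysis set is named, but the analysis plan is not shown and the article is a condensed account, so that silence is no fault in itself. A reader might infer that removed patients are excluded from the tests; the document does not say so. This stands, and it is why the point concerns the rule and the follow-up it leaves open.

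A reader might also infer that removal is driven by response and that the comparison is therefore biased. No passage says this. The nearest are the Procedure section, which tells patients that effects take time so as to encourage follow-up, and the Control group section, which links slow results with the need to avoid dropouts. They make a link plausible and no more. Patients are blinded, and controls do have needles placed in the abdomen, so the arms may behave alike.

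Larger effects can be produced by assumption. A 1-point bias from equal 20% removal in both arms, outcome-related in one, needs D = 1.0/0.20 = 5 points on a 0–10 scale. That is too strong to rest a conclusion on.

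Finally, since the control group receives SA, the term 'EA sessions' could be read as confining the rule to the EA arm. Loose drafting is more likely: the schedule is the same in both arms, dropouts are spoken of in both, and blinded researchers could not apply a one-arm rule.

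**Conclusion.** The point holds as a possibility of bias built into a stated rule. As written, the natural reading is that a patient who misses two consecutive sessions leaves the study, with no provision for collecting the 12-week outcome. In month 1 that can follow from a single missed week.

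The size and sign of any bias cannot be derived from the protocol. The range of about 0.2–0.7 VAS points, against a 3-point target, rests wholly on the assumed removal of 10–30%, a correlation of 0.3–0.5, and arms that differ in removal rate or mechanism. Where they do not differ, or removal is unrelated to outcome, there is none. The documents support neither a claim that the comparison is biased nor one that it is tilted towards EA.

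**What to change.** Amend the Removal criteria section so that it:

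- states that missing sessions does not end outcome follow-up;
- asks all randomised patients in both arms for VAS, WOMAC and medication use at 1, 3, 6 and 12 months, unless they withdraw consent to data collection;
- says how this is done off schedule: VAS at a visit or on a posted form, since it is a mark on a 10-cm line, while the orally answered WOMAC may be done by telephone;
- states that all randomised patients are analysed in the group assigned, or refers to the analysis plan if that already says so;
- replaces 'EA sessions' with 'study sessions', so that the rule clearly covers both arms.

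Whether and when sessions stop is a clinical matter for the sponsor and is not addressed here.

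The cost is one paragraph, some extra follow-up effort, and a somewhat diluted effect if non-attenders gain nothing. Recruitment was under way when the article was written, so any removal before the change may lose a primary outcome for good.
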